**8.3 HEALTH ECONOMIC ANALYSIS**

**Objective:** To determine the cost-effectiveness of immediate PCI compared to standard management of patients presenting with N-STEMI ACS.

**Methods:** Costs will be estimated from the perspective of the UK National Health Service (NHS). The following data will be extracted from study case report forms (CRFs): the costs associated with the PCI procedure and any staged procedures, procedure time and consumables/equipment e.g. use of GP IIb/IIIa inhibitors and stents), index admission hospital length of stay, including time in coronary care unit/cardiac intensive care. We anticipate the timing of procedures to be an important cost-driver, if more participants in the immediate procedure group received their treatment out of hours. To monitor the cost implications of this, we will conduct a survey to establish on-call scheduling at each site. Cardiac hospital out-patient appointments and hospital readmissions will be monitored up to 12 months follow-up. The in-hospital site of in-patient management will be documented. Unit costs will be assigned to each item of resource use for a standard price year. This will enable the mean cost associated with each treatment option to be estimated.

**Clinical** (a composite of all-cause mortality, new myocardial infarction and re-admission with heart failure) and quality of life outcome data will be collected. The latter will be based on the EQ-5D-5L (1) and estimated within 24-hours of procedure (alongside formal consent) and at 6 month and 12 month follow-up, enabling QALY (quality-adjusted life year) scores to be derived.

Multiple imputation (dependent on the level of missing data) and regression analysis will be undertaken to estimate the mean difference in cost between the two groups (mean incremental cost) and the mean incremental effect (the mean difference in both the total number of composite events / QALYs). Assuming dominance does not occur (where one option is estimated to be more effective and less costly than the other option), the

RAPID-NSTEMI

[figure not shown]

incremental cost-effectiveness ratio for both the composite clinical outcome and QALYs will be estimated and assessed in relation to a range of cost-effectiveness thresholds e.g. £20,000-£30,000 per QALY is recommended by NICE (31). The associated level of uncertainty will also be characterised by estimating the probability of each treatment option being cost-effective according to the cost-effectiveness acceptability curve (CEAC) (32). Sensitivity analysis will also be undertaken to assess the robustness of conclusions to changes in key assumptions. All analysis will initially be conducted on an intention-to-treat basis, with sensitivity analysis subsequently comparing trial treatment received per protocol (very early intervention with delayed/standard intervention).

RAPID-NSTEMI[figure not shown]

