#### 7.2.2 Secondary Outcome Measures

- Individual components of the primary end-point within 12 months:
  - Incidence of all-cause mortality within 12 months
  - Incidence of new myocardial infarction within 12 months
  - Incidence of admission for heart failure within 12 months
- Incidence of cardiovascular mortality within 12 months
- Length of in-patient stay (defined as randomisation to first discharge) in days
- Events prior to planned procedure:
  - Incidence of all-cause mortality prior to planned coronary angiography following index admission with NSTEMI
  - Incidence of new myocardial infarction prior to planned coronary angiography following index admission with NSTEMI
  - Incidence of major bleeding (classified as BARC 3-5) prior to planned coronary angiography following index admission with NSTEMI
- Incidence of admission for ischaemia-driven revascularisation within 12 months
- Incidence of admission for any cause within 12 months
- Quality of life measured using Seattle angina score at 24 hours post procedure, 1 month, 6 months and 12 months
- Quality of life as assessed using the EQ-5D-5L questionnaire at 24 hours post procedure, 1 month, 6 months and 12 months
- Incidence of BARC 3-5 classified bleeding as in-patient, and up to 12 months
- Incidence of stroke within 12 months

RAPID-NSTEMI[figure not shown]

- Cost effectiveness of immediate PCI versus standard care
- Left ventricular ejection fraction (LVEF) and infarct size on cardiac MRI scan\*
- Sensitivity and specificity of novel biomarkers in predicting which patients do or do not require PCI following diagnostic angiography\*\*
- Proportion of patients needing emergency/urgent revascularisation (in group B)
- Incidence of total VARC-2 classified access site complications as in-patient, and up to 12 months
- Incidence of major VARC-2 classified access site complications as in-patient, and up to 12 months

\*Additional CMR outcomes are specified in the CMR substudy protocol (appendix V)

\*\* Additional biomarker outcomes are specified in the Biomarkers substudy protocol (appendix VI)

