#### 7.3.2 Exclusion Criteria

- ST elevation myocardial infarction
- Evident type 2 myocardial infarction (e.g. anaemia)
- Evidence of previous known cardiomyopathy
- Cardiogenic Shock
- Known severe valvular heart disease
- Need for urgent PCI according to ESC Guidelines (haemodynamic instability, VT/VF, recurrent or persistent pain)
- Any contraindication to PCI
- Current participation in another intervention trial

RAPID-NSTEMI

[figure not shown]

Figure 2: Patient Flow to Randomisation

[figure not shown]

\*or written consent, depending on local regulatory guidelines (applicable to sites in Northern Ireland/Scotland only)

RAPID-NSTEMI[figure not shown]**7.4 TRIAL INTERVENTIONS**

If the initial clinical eligibility for N-STEMI criteria are suspected, blood is drawn for Hs-Troponin immediately (i.e. as close to admission as possible). If this returns raised according to individual hospitals criteria then a GRACE 2.0 score is calculated at that time. A GRACE 2.0 score of  $\geq 118$ , or  $\geq 90$  with additional high risk features - see inclusion criteria, will lead to patient ASSENT (or written informed consent, depending on local regulatory guidelines. Further details are provided in section 7.6) and if confirmed then randomisation providing there are no exclusion criteria. If the initial Hs-Troponin is reported as normal, a second sample may be taken at 3 hours in line with current European guidelines. If elevated, the participant may be randomised if all other criteria met. Randomisation will be performed using an independent Interactive Voice Response System randomisation system (Sealed Envelope Ltd), the patient will be randomised to either Group A or B. The participant trial number will be documented.

**GROUP A:** Immediate angiography with follow-on revascularisation if indicated - transfer to the catheter laboratory should be performed as soon as possible, and is recommended but not mandated within 90 minutes of randomisation

**GROUP B:** Standard angiography with follow on revascularisation if indicated, - within Guideline recommended times.  
Standard interim therapy such as LMWH/DAPT will be mandated in this group until angiography.

All interventional procedures will be undertaken according to current best practice (e.g. peri-procedural intravenous heparin, radial approach as preferred access site, and use of drug-eluting stents). Patients in Group B who suffer the following:-

- on-going chest pain,

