**7.8 INTERVENTION**

If randomised to immediate angiography (+/- intervention), the patient will be transferred to the cardiac catheterisation lab with no further avoidable delay similar to those on a STEMI pathway. At angiography the interventionist will decide, in accordance with usual criteria whether the patient should receive revascularisation (PCI or CABG) or whether they need no further management due to absence of flow limiting coronary obstruction, or whether the disease should be treated with medication alone. Routine practice including use of FFR to inform the clinician will be expected. All decisions will be documented in the eCRF. If the

RAPID-NSTEMI

[figure not shown]

appropriate intervention is PCI, then all things being equal the procedure will be completed at that sitting.  
Planned management of any non-infarct related artery (N-IRA) disease will be allowed and documented as being planned at the time of the first intervention.

If randomised to Group B the patient will be managed on an appropriate acute ward and receive subcutaneous LMWH, DAPT (Aspirin plus Ticagrelor/clopidogrel), and secondary prevention medication as per standard practice, including high dose statins. These patients will be listed for coronary angiography as per current standard care for N-STEMI patients for that hospital.  
Planned management of any N-IRA disease will be allowed and documented as being planned at the time of the first intervention.  
A screening log of potentially eligible but non-included patients with reasons, will be kept and reviewed regularly by the trial management group, screening log data will also be included in the reports to both the TSC and DSMC.

If the immediate Troponin is negative, patients will be considered to be suffering unstable angina and are NOT eligible for randomisation and will be managed according to the responsible physician standard of care for such patients. A second sample may be taken at 3 hours in line with current European guidelines, and if elevated, the participant may be randomised.

All patients will be approached as soon as possible following randomisation for formal consent to remain in the study: a patient information sheet and a consent form for signature will be given to the participant. Once written consent has been obtained participants allocated to group A will complete a quality of life baseline form (EQ-5D-5L).

A repeat Troponin will be undertaken within 24 hours after PCI.

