### 7.11 PROCEDURES AT DISCHARGE

At discharge patients will have an ECG, the study case report form will be completed. The EQ-5D-5L and Seattle Angina Questionnaire will be completed within 24-hour post PCI in both groups.

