**Follow up at 30 days +/- 1 week**

Patients will be contacted by telephone at 30 days +/- 1week. Information on clinical progress and especially on readmission, further investigations, EQ-5D-5L and Seattle Angina Questionnaire and changes to medication will be documented. A complete list of medication being taken will be recorded.

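### Section 8.3 leaves the 30-day EQ-5D-5L out of the QALY time points, so a post-procedure first value, unequally timed by arm, carries about six times the weight it needs to

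*Protocol*

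**What the plan says.** On the QALY time points, section 8.3 says that quality of life will be "estimated within 24-hours of procedure (alongside formal consent) and at 6 month and 12 month follow-up, enabling QALY" scores to be derived. It plans regression, multiple imputation depending on the level of missing data, and sensitivity analysis on key assumptions. It names no interpolation rule, time origin or covariates.

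On what is collected:
- Section 7.2.2 lists "Quality of life as assessed using the EQ-5D-5L questionnaire at 24 hours post procedure, 1 month, 6 months and 12 months".
- Section 7.14 includes the questionnaire among the items recorded at the 30-day call: "Information on clinical progress and especially on readmission, further investigations, EQ-5D-5L and Seattle Angina Questionnaire".
- Table 2 marks the EQ-5D-5L within 24 hours after angiography, at 30 days, at 6 months and at 12 months.

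On the first form:
- Section 7.11 says "The EQ-5D-5L and Seattle Angina Questionnaire will be completed within 24-hour post PCI in both groups", and Table 1 agrees. Table 2 anchors it to angiography instead.
- Section 7.8 says that, after written consent, "participants allocated to group A will complete a quality of life baseline form (EQ-5D-5L". It says nothing about Group B.
- Neither table schedules an EQ-5D-5L before the procedure.

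On timing of the procedure, section 7.4 says of Group A that "transfer to the catheter laboratory should be performed as soon as possible, and is recommended but not mandated within 90 minutes of randomisation". For standard care it cites audit medians of 60.8 hours from admission for direct admissions and 82.1 hours for inter-hospital transfers.

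**The concern.** There are two linked problems.

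**Omitted time point.** Section 8.3 gives a specific list of EQ-5D-5L points for QALYs, and it is shorter than the list collected everywhere else. A health economist who follows 8.3 has nothing between the day after the procedure and 6 months. The treatments differ only in the first days, so the first month is a natural place to look for a difference. Section 6.0 describes an earlier trial of immediate intervention in which the whole difference in death or new infarction arose within 30 days. That evidence concerns clinical events, not utility, but it shows why the early window should not be left unmeasured.

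**First value.** It is taken after the procedure, so it may already reflect treatment, and it falls at a different time since randomisation in each arm. Section 7.8 labels it a baseline, which invites its use as one. With 30 days left out, this value also determines a large share of the QALY total.

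What is at stake is the incremental QALY, and so the cost-effectiveness ratio. Section 4.0 says the economic analysis gains importance if clinical outcomes turn out equal. Small QALY differences would then matter more.

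**Working it through.** The protocol states no QALY figure, so there is none to reproduce. Two assumptions apply throughout: the trapezoid rule, because 8.3 names no method, and every utility value, because the protocol gives none. The threshold of £20,000-30,000 per QALY is from section 8.3.

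**1. Weight of each questionnaire, in years.** Under the trapezoid rule, each value is weighted by half the span between its neighbours. Here the first form is placed at time 0 and 30 days is 30/365.25 = 0.0821 year.

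| Schedule | First form | 30 days | 6 months | 12 months |
|---|---|---|---|---|
| Section 8.3 (three points) | 0.25 | – | 0.50 | 0.25 |
| As collected (four points) | 0.0821/2 = 0.041 | 0.50/2 = 0.25 | (1 − 0.0821)/2 = 0.459 | 0.25 |

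Including 30 days cuts the first form's weight by a factor of 0.25/0.041, about 6. The 30-day visit window is ±1 week. At day 23 the first form's weight would be 23/365.25/2 = 0.031, and at day 37 it would be 0.051. The 30-day weight stays at 0.25 either way.

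**2. Difference present only at 30 days.** Suppose the arms differ by *e* at 30 days and not at the other points. The three-point schedule records nothing, and the amount lost is 0.25 × *e*.
- *e* = 0.03: 0.25 × 0.03 = 0.0075 QALY, or £150-225 per patient.
- *e* = 0.05: 0.25 × 0.05 = 0.0125 QALY, or £250-375 per patient.

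**3. Timing of the first form.** In Group A, recommended transfer at up to 1.5 h plus up to 24 h gives about 25.5 h after randomisation, roughly day 1. In Group B, the direct-admission median of 60.8 h plus up to 24 h gives about 84.8 h after admission, roughly day 3.5. If this timing alone made the first utilities differ by an assumed 0.05, the incremental QALY would move as follows.
- Three points: 0.25 × 0.05 = 0.0125 QALY.
- Four points: 0.041 × 0.05 = 0.0021 QALY.

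**4. Group B's wait itself.** The gap between procedures is 60.8 − 1.5 = 59.3 h if randomisation is at admission, or 53.3 h if it is at the 6-hour limit. Taking the longer, 59.3/(24 × 365.25) = 0.0068 year. At assumed utility differences of 0.1 to 0.3 during the wait this is 0.0007 to 0.0020 QALY, about £14 to £61. With the transfer median (80.6 h) it is 0.0009 to 0.0028 QALY. This is small.

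**5. Early recovery within an arm.** Suppose utility rises by an assumed 0.10 within 30 days and then stays level. A line drawn to 6 months understates that patient's QALYs by 0.5 × 0.10 × 0.5 − 0.5 × 0.10 × 0.0821 = 0.025 − 0.0041 = 0.021. This is a per-patient amount, not a difference between arms.

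**The case against.** The strongest reply is that 8.3 is an incomplete list and not an analysis decision. It does not say the 30-day value will be excluded, the rest of the protocol schedules it, and a separate health economics team will do the work. That is fair as to intent, and a drafting slip is plausible. It does not remove the point, because 8.3 ties QALYs to three named times and conflicts with 7.2.2, Table 2 and 7.14.

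A reader might also infer stronger claims that the documents do not support:
- **That a straight line from 24 hours to 6 months is planned.** Section 8.3 names no method, so the figures above depend on the trapezoid assumption.
- **That the first value will be used as a baseline covariate and will bias the result.** Section 8.3 mentions regression without naming covariates. Only 7.8 uses the word baseline.
- **That early recovery biases the comparison by 0.021 QALY.** That amount cancels if both arms recover alike. Only a difference between arms matters.
- **That leaving out Group B's wait is a serious loss.** It is worth about 0.0007 to 0.0020 QALY.
- **That Group B gets no first form.** Section 7.11 and Table 1 give it to both groups. Section 7.8 is an inconsistency to tidy.
- **That section 4.0 makes cost-effectiveness decisive.** It says the analysis would become more important, and its reason is length of stay, not early utility.

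It is also true that a pre-procedure questionnaire would be hard to obtain in Group A, given verbal assent at most sites and rapid transfer. None is asked for here.

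**Conclusion.** The point holds as an inconsistency with a measurable consequence. As written, 8.3 omits a collected value that would carry a 0.25-year weight. It also leaves a 0.25-year weight, instead of about 0.041, on a first value that is post-procedure and unequally timed by arm. For assumed between-arm utility differences of 0.03 to 0.05 confined to 30 days, the loss is 0.0075 to 0.0125 QALY per patient, or £150 to £375 across the quoted thresholds.

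These sizes rest on the trapezoid rule and on assumed utilities. They show what could be missed and do not predict that it will be. The direction of any error is unknown. Only the secondary cost-effectiveness outcome is affected, not the primary endpoint or the sample size. The correction is worth making because it costs almost nothing.

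**What to change.** In section 8.3:
1. Add the 30-day EQ-5D-5L to the time points used for QALYs.
2. Count QALYs from randomisation and place each questionnaire at its actual date.
3. State that the first form is a follow-up value and not a pre-treatment baseline.
4. State how utility from randomisation to that form is set, using the same rule in both arms, and vary it in sensitivity analysis. A common assumed starting utility is one option among several.

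Elsewhere, reconcile section 7.8 (Group A only, labelled baseline) with Table 1, Table 2 and section 7.11 (both groups, after the procedure). Settle at the same time whether the form is anchored to angiography (Table 2) or to PCI (Table 1 and 7.11). Appendix VI expects only about two-thirds of patients to need PCI, so the choice affects many participants.

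The cost is wording in 8.3, 7.8 and any health economics plan. No new data are needed. The one drawback is an assumption about utility before the first form, and section 8.3 already provides for sensitivity analysis on key assumptions.

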## 9.0 DATA MANAGEMENT

### 9.1 DATA ENTRY

Data entry will be conducted by the study delivery team at site. Case report forms (CRFs) will be maintained in electronic form on a validated web based Remote Data Capture (RDC) system called InferMed MACRO provided by the LCTU. Access to the electronic CRF will be for authorised study personnel using their individual access codes. The investigator and designated personnel must ensure accuracy, completeness and timeliness of data reported in the eCRF and all required reports. Data reported on the eCRF that are derived from source documents should be consistent with the source documents or the discrepancies should be explained.

### 9.2 DATA PROTECTION

Participant's personal data included in study related databases, shall be treated in confidence and in compliance with all applicable laws and regulations. When processing or archiving personal data, the Sponsor or its representative shall take all appropriate measures to safeguard and prevent access to this data by any unauthorised third party. Consent for NHS Number, DOB and gender sex to be used in order to obtain data linkage for NHS Digital will be specifically requested.

### 9.3 CONFIDENTIALITY

Each participant will be assigned a unique identification number upon recruitment. The database will be password protected and only researchers collecting data will have access. All personalised information for participants will be kept confidentially at the recruiting site unless there is specific consent and HRA approval for transfer of this to another site for study related purposes.

Paper copies of case report forms (signed eligibility criteria and randomisation CRFs) and questionnaires will be stored in a locked filing cabinet in the relevant research office. Neither hard copies nor electronic files containing personal information will be removed from the research office or stored in a non-secure manner electronically. The study research team will comply with the Data Protection Policy of the UHL, UoL and local NHS Trusts.

### 9.4 DATA ACCESS

All source data, study documents, participant notes will be made available for monitoring, audits and inspections by the appropriate regulatory bodies, Ethics Committee, the Sponsor, funders, LCTU and members of the Research Governance Team.

All electronic data will be stored on secure network systems, to which only the relevant study staff have access, which is granted by the IT services or the research team. These systems are backed up daily by the UoL IM&T.

### 9.5 ARCHIVING

On termination of the trial, the study documents are to be archived until at least 15 years after the last reporting of data in an official manuscript.

RAPID-NSTEMI[figure not shown]

## 10.0 TRIAL ORGANISATION, REGULATION AND OVERSIGHT

### 10.1 FUNDING SOURCES

The study has been funded by grants from the British Heart Foundation (BHF Clinical Study CS/17/1/32445). Additional support and resources for the trial will be provided by the participating Trusts and their corresponding Comprehensive Local Research Networks (CLRN).

### 10.2 ETHICAL CONSIDERATIONS

The trial will be conducted according to ICH GCP, relevant regulations and the SOPs and quality management procedures of Sponsor, host organisations and LCTU. Ensuring adherence to the principles of the Medical Research Council Good Clinical Practice guidelines, relevant Data Protection legislation, UK Policy Framework for Health and Social Care Research, Health Research Authority (HRA) regulations and relevant local and national laws. Ethical aspects will be conducted in accordance with the Declaration of Helsinki (Revised 48th General Assembly, Somerset West, Republic of South Africa, October 1996, <http://www.wma.net/>).

### 10.3 SPONSOR

The Sponsor is the University Hospitals of Leicester NHS Trust (UHL). The trial sponsor provides ultimate approval of all new versions of the protocol before they become live. UHL will be undertaking the monitoring of the trial, including site monitoring visits and source data verification.

### 10.4 HEALTH RESEARCH AUTHORITY (HRA) APPROVAL

This protocol and associated documents e.g. assent forms, patient information sheets, consent forms, study posters and any amendments to these will be submitted to the Health Research Authority (HRA) and Research Ethics Committee (REC) for ethical approval.

